### 10.3 Secondary Analysis of Primary Endpoint(s)

The secondary analysis of the primary endpoint will compare which of the two algorithms between study conditions has superior performance characteristics for detecting early or asymptomatic SARS-CoV-2 indication or infection. Time-to-event analyses will be performed using the Intention-to-treat, Efficacy analysis and Partial compliance set. Analyses will be performed within each study period and stratified per risk group. Kaplan-Meier plots will be

constructed for visual support. An event will be defined as either the first indication (red-light indicator from the Ava COVID-RED app) or first infection (as confirmed by PCR/antigen testing) of SARS-CoV-2 of a subject during the study period. Subjects lost to follow-up or reaching the end of the period without infection will be censored. Stratified log-rank tests will be performed within each period to assess whether the experimental condition shows a statistically significant improvement (or lack thereof) in time to indication or infection as compared to the control condition with a median difference used to state the effect size. If the median is not yet reached in either study condition then a different quantile will be used. If other variables are to be taken into account, Cox proportional hazards models will be used where assumptions are met.

This same analysis will also be performed retrospectively in all subjects where the time to first indication or infection will be assessed using the algorithm based on only the symptoms data or both the symptoms and bracelet data within each subject. Because the measurement methods are correlated (both physically and in data collection), a within-person comparison can be made using paired statistical methods. If assumptions are satisfied, a Wilcoxon signed rank test will be used for this analysis; otherwise, other paired tests will be considered.

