## 2. OBJECTIVES

### 2.1 Primary Objectives:

Using laboratory-confirmed SARS-CoV-2 infections (detected via serology tests, PCR tests and/or antigen tests) as the gold standard, we will determine the sensitivity, specificity, positive predictive value (PPV) and negative predictive value (NPV) for each of the following two algorithms to detect *first-time* SARS-CoV-2 infection including early or asymptomatic infection: the algorithm using Ava Bracelet data when coupled with the self-reported Daily Symptom Diary data, and the algorithm using self-reported Daily Symptom Diary data alone. In addition, we will determine which of the two algorithms has superior performance characteristics for detecting SARS-CoV-2 infection including early or asymptomatic infection as confirmed by SARS-CoV-2 virus testing.

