### 3.4 Algorithm indicators

In both study conditions, the respective algorithms will alert subjects about their real-time health status in the Ava COVID-RED app through 3 types of indicators:

- **Green light:** No deviations in physical health (symptoms or biophysical parameters) detected. No recommendation is given to the subjects.
- **Yellow light:** Subjects are experiencing some symptoms but not those strictly defined as related to COVID-19 or biophysical parameters deviate slightly from baseline but do not meet the threshold value for a Red light indicator. The Yellow light indicator asks participants to consider self-isolating and keeping an eye on the Ava COVID-RED app the following day.
- **Red light:** Significant changes in biophysical parameters have been detected or symptoms that meet the RIVM criteria have been reported. The Red light indicator suggests subjects consider getting tested for COVID-19 and/or to consult a medical professional.

In all cases of a red-light indicator, subjects will receive the following generic message on the home screen of the Ava COVID-RED app after synchronising their bracelet or logging their symptoms within the last 24 hours:

“Your data suggests changes in physiological parameters and/or symptoms that might be related to a potential COVID-19 infection. Please consider seeking testing and/or input from a medical professional.”

When subjects obtain a positive PCR/antigen or serology test result during the study, they will continue to be in the study but will be moved into a so-called “COVID-positive” mode in the Ava COVID-RED app. This means that they will no longer receive recommendations from the algorithms but can still contribute and track symptom and bracelet data.

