#### 4.4.2 Early detection analysis

The second statistical analysis that will be performed for the primary objective concerns the timing of each study condition to detect SARS-CoV-2. The time to first SARS-CoV-2 indication or infection will thus be compared between the conditions. This will be tested using a stratified log-rank test. Frequently, power calculations for the log-rank test assume some form of proportional hazards or a specific parametric family for the study arms. In this study, we expect the experimental condition to be able to detect SARS-CoV-2 infection earlier due to the possible detection of pre- or asymptomatic individuals due to deviations in physiological parameters. However, when subjects become symptomatic, the algorithms in both the control and experimental condition will each declare subjects to likely be infected at the same moment by definition. To account for this aspect, a piecewise log-rank test power calculation is used to characterize the trial power. The assumption in the piece-wise hazards is that initially the experimental condition will have a higher chance to detect SARS-CoV-2 infection; however, this difference will decrease over time resulting in equal hazards in the later pieces of the hazard function. As described in the first analysis above, the proposed crossover design results in an application of bootstrap statistical testing so that the power calculations in Table 5 are rough approximations. The estimated power is bounded below by a parallel-arm study with 10,000 subjects per condition and above by a study with 20,000 subjects per condition. From these bounds it appears that the trial is well powered under all of the recently reported RIVM data.

Table 5: Lower (10,000) and upper (20,000 ) bounds of the trial power for a piecewise log-rank test to detect differences between study conditions on the time to first SARS-CoV-2 indication or infection based on infection rates of Weeks 36 through 40 of 2020

|              | Week 36 |      | Week 37 |      | Week 38 |      | Week 39 |      | Week 40 |      |
|--------------|---------|------|---------|------|---------|------|---------|------|---------|------|
|              | 10k     | 20k  | 10k     | 20k  | 10k     | 20k  | 10k     | 20k  | 10k     | 20k  |
| Power | 0.66    | 0.92 | 0.80    | 0.98 | 0.94    | 0.99 | 0.99    | 1.00 | 1.00    | 1.00 |

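### The Section 10.3 time-to-event analysis counts any first red light in any subject as an event, so it mainly compares alarm frequency, not earlier detection of confirmed infection

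*Protocol*

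**What the plan says.** Section 4.4.2 calls time to first indication or infection the second analysis for the primary objective. Section 10.3 fixes how it is done:

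- Event: "An event will be defined as either the first indication (red-light indicator from the Ava COVID-RED app) or first infection" confirmed by PCR or antigen test. Nothing requires the red light to be followed by a confirmed infection.
- Population: "Time-to-event analyses will be performed using the Intention-to-treat, Efficacy analysis and Partial compliance set". It is not limited to infected subjects.
- Censoring: "Subjects lost to follow-up or reaching the end of the period without infection will be censored".
- Interpretation: a stratified log-rank test is used "to assess whether the experimental condition shows a statistically significant improvement (or lack thereof) in time to indication or infection". The same analysis is then repeated retrospectively within subjects, with a Wilcoxon signed rank test if its assumptions hold.

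The objective in Section 2.1 is superior performance in "detecting SARS-CoV-2 infection including early or asymptomatic infection as confirmed by SARS-CoV-2 virus testing".

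Section 3.4 gives the triggers for a red light: "Significant changes in biophysical parameters have been detected or symptoms that meet the RIVM criteria have been reported". Section 4.4.2 says that once a subject has symptoms, "the algorithms in both the control and experimental condition will each declare subjects to likely be infected at the same moment by definition". It describes the hazards behind Table 5 in terms of infection: "initially the experimental condition will have a higher chance to detect SARS-CoV-2 infection; however, this difference will decrease over time".

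**The concern.** Neither trigger is specific to SARS-CoV-2. Section 3.3 includes ordinary cold symptoms, and Section 1 concedes that temperature and pulse changes are not specific to COVID-19. Uninfected subjects will therefore supply many of the events. If one algorithm alarms more often in them, its curve falls faster and the test reads this as earlier detection. If it alarms less often, it looks slower even when it finds infections sooner.

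Earlier detection is the project's stated main purpose (Section 1). A significant log-rank result, in either direction, could be reported as evidence on that question when it mostly reflects the false-alarm rate.

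**Working it through.** **1. Inputs.** From the protocol: 10,000 per condition (lower bound, Section 4.4.2), 3 months per period (90 days used), two-sided 0.05 (Section 10), and false-alarm differences of 1.5 and 3 points (the specificity differences in Table 4). Infection rates are positives divided by tested in Table 2: 3.01%, 4.00%, 5.91%, 7.99% and 10.42% for Weeks 36–40.

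Assumed, because the protocol does not state them: sensitivity 0.8 in both arms; missed infections test positive 4 days later; baseline false-alarm probability 17% per period, with a range of 10–50%. The 17% follows from the specificity of about 0.82–0.835 that reproduces the powers in Table 4.

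**2. Table 5 first.** The piecewise hazards are not given, so Table 5 cannot be reproduced exactly. As a consistency check, take infected subjects as the only events, D = 2 × N × infection rate, and one constant hazard ratio:

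power = Φ(ln HR × √(D/4) − 1.96)

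For Week 36 at 10,000, D = 602. With HR = 1.2175, ln HR = 0.1968, and 0.1968 × √150.5 − 1.96 = 0.45, so power is about 0.68. All cells (10k / 20k):

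| Week | Table 5 | Infections only, HR 1.2175 |
|---|---|---|
| 36 | 0.66 / 0.92 | 0.68 / 0.93 |
| 37 | 0.80 / 0.98 | 0.79 / 0.98 |
| 38 | 0.94 / 0.99 | 0.92 / 1.00 |
| 39 | 0.99 / 1.00 | 0.98 / 1.00 |
| 40 | 1.00 / 1.00 | 0.99 / 1.00 |

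Before rounding, all ten cells agree within 2 points. Now count false red lights as events too, D = 20,000 × [p + (1 − p) × f], and match Week 36 to 0.66 (so ln HR × √(D/4) = 0.41 + 1.96 = 2.37). At f = 17%, D is 3,900 in Week 36 and 5,130 in Week 40. Week 40 power is then Φ(2.37 × √(5,130/3,900) − 1.96) = Φ(0.76) = 0.78. Over f = 10–50% it is 0.83 down to 0.69, against 1.00 in Table 5. Table 5 behaves as if only infections were events, which is not the event in Section 10.3.

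**3. Hand check of the effect of false alarms.** Raise the false-alarm probability from 17% to 18.5% and leave detection of infection identical. In uninfected subjects HR = ln(0.815)/ln(0.83) = 1.098, so ln HR = 0.0934. At 3.0% infected the simulation has about 4,038 events, 85.2% of them in uninfected subjects. The diluted effect is about 0.0934 × 0.852 = 0.0796, and Φ(0.0796 × √(4,038/4) − 1.96) = Φ(0.57) = 0.71.

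**4. Simulated daily log-rank test, event as written** (risk strata ignored; 400 runs per cell in the main set). Entries give how often the experimental arm is declared significantly earlier, or significantly later where stated:

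| Scenario | 17% baseline | Baselines 10–50% |
|---|---|---|
| Identical detection, +1.5 points false alarms | 71% (3.0% infected), 58% (10.4%) | 50–84% |
| Identical detection, +3 points | 99–100% | 97–100% |
| True 2-day lead, equal false alarms | 2–3% | 1–4% |
| True 2-day lead, 3 points fewer false alarms | declared later: 99–100% | declared later: 96–100% |

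The nominal error in one direction is 2.5%. Repeat simulations at the 17% baseline gave 59–73% for the first row and up to about 5% for the third. Uninfected subjects supply 76–94% of events at 3.0% infected and 46–81% at 10.4%.

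**5. Effect of restricting to confirmed infections.** With infected subjects only, a first red light in an assumed 14-day window before confirmation, and a rank-sum test (1,000 runs), 1.5–3 extra points of false alarms and no true lead gave 2–5% false declarations. A true 2-day lead in only 25% of detected cases was found in 96–100% of runs. This check held the confirmation date fixed regardless of the red light. It supports the restriction and says nothing about which time anchor to use.

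**The case against.** **False alarms are visible elsewhere.** Section 10.2 estimates specificity and PPV, and Section 10.5 compares the proportions ever red. This stands, so a reader should not infer that the trial as a whole would be won by an uninformative bracelet. But nothing in Section 10.3 makes its conclusion depend on those results.

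**The intent may have been infections only.** The censoring sentence and the hazard description in Section 4.4.2 both speak of infection. Part of the fault may therefore be unreconciled wording. Still, an uninfected subject with a red light has already had an event under the definition, so the censoring sentence contradicts it and does not restrict the population.

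**The bias need not favour the bracelet.** A reader might infer that experimental red lights always contain the control ones, so that added alarms can only help and the paired test cannot favour control. That follows if Sections 3.4 and 4.4.2 hold literally. Section 3.3, however, describes a deterministic symptom rule for control and a separate machine-learning algorithm for the experimental condition. Nothing says that the retrospective versions with and without bracelet data are nested. Without nesting the bias can run either way.

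**The SAP may add detail.** It may, but the event and the population are fixed in this protocol.

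**Conclusion.** The concern holds. As written, the log-rank test and its paired repeat mainly compare alarm frequency and do not answer the Section 2.1 question. With identical detection of infection and 1.5 points more false alarms, the experimental arm is declared earlier in about 58–73% of runs at an assumed 17% baseline (50–84% over 10–50%). A real 2-day lead with equal false alarms is found at about chance level. A real lead with fewer false alarms is declared worse. These sizes rest on the assumed baseline rate, sensitivity and test delay; the direction held over every baseline tried.

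If symptoms trigger both algorithms simultaneously, as Sections 3.4 and 4.4.2 say, extra bracelet alarms can only favour the experimental condition. Section 3.3 does not guarantee this.

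Two further inferences are not supported. Uninfected subjects do not supply most events in every scenario (46% at the lowest). Nor can it be said that an infections-only analysis would have less power than Table 5, which already behaves like one. The Table 5 finding is a consistency check with one fitted hazard ratio and does not reproduce the sponsor's calculation.

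**What to change.** Change Section 10.3 as follows:

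- Restrict the time-to-detection comparison and the paired analysis to subjects with confirmed infection in the period.
- Count only a first red light inside a pre-set window around the infection. Score none in the window as not detected.
- Anchor timing on symptom onset in symptomatic cases. Use the positive-sample date only as a sensitivity analysis: red lights prompt testing (Sections 3.5, 8.4.11 and 8.4.12), so that date moves with the alarm.
- For asymptomatic or serology-only infections, compare detected with not detected and give no lead time.
- In the retrospective paired analysis, compare the two algorithms' first red-light dates within the same infected subject and window. This needs no test date.
- Report red lights in never-infected subjects separately, for example per person-time.
- Correct the censoring sentence to agree with the event, and restate Table 5 for that event with the piecewise hazards given.

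Cost: protocol and SAP wording plus a new power calculation. Fewer subjects contribute, and timing cannot be estimated for asymptomatic or serology-only infections. Power must be restated, and whether it rises or falls is not established.

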#### 10.4 Synthesis of evidence

To benefit from the crossover design and synthesize the results of a chosen test statistic over both study periods, it has to be taken into account that there is a missing-data mechanism by design. Subjects with SARS-CoV-2 infection in the Learning Phase will have their data excluded from Period 1 and Period 2. Likewise, Subjects with SARS-CoV-2 infection in Period 1 will have their data excluded from Period 2. As such, traditional crossover analysis methods and adjustments for missing data are not sufficient and bootstrap methods will be used. To indicate how the bootstrap approach can be used it is illustrated for the ever-infected analysis mentioned in section 10.2. Table 6 shows example data for the ever-infected analysis from which **predicted condition positive**, **predicted condition negative**, **condition positive**, and **condition negative** can be derived.

Table 6: Example data for ever infected analysis

| UID    | Condition
Period 1 | Observed
outcome
P1 | True
outcome
P1
(serology) | Condition
Period 2 | Observed
outcome
P2 | True
outcome
P2
(serology) |
|--------|-----------------------|---------------------------|-------------------------------------|-----------------------|---------------------------|-------------------------------------|
| 1      | 1                     | 0                         | 0                                   | 0                     | 0                         | 1                                   |
| 2      | 0                     | 1                         | 1                                   | NA                    | NA                        | NA                                  |
| 3      | 1                     | 0                         | 1                                   | NA                    | NA                        | NA                                  |
| ...    |                       |                           |                                     |                       |                           |                                     |
| 20,000 | 0                     | 0                         | 0                                   | 1                     | 1                         | 1                                   |

#### 10.4.1 Bootstrap approach

Using data from Table 6, sample statistics, denoted by  $s_{ij}$ , can be calculated, where  $i = 1$  denotes the experimental condition,  $i = 2$  the control condition,  $j = 1$  study Period 1 and  $j = 2$  study Period 2 (see Table 7). The sample statistics in question could be sensitivity or specificity for instance. In a normal statistical analysis, distributional assumptions are used to provide uncertainty about the sample statistics obtained in the study. A bootstrapping approach does not require these distributional assumptions.

Bootstrapping is a resampling method in which sample statistics are calculated multiple times using new samples drawn with replacement from the original dataset. This leads to an empirical distribution of the sample statistics which can be used to quantify the uncertainty. In the current study, paired observations are drawn (i.e. both the outcome of Period 1 and Period 2 are jointly sampled for each subject).

Table 7: Notation of statistics per arm and period

|                        | Period 1               | Period 2               |
|------------------------|------------------------|------------------------|
| Sequence 1             | Experimental Treatment | Control Treatment      |
| Sequence 2             | Control Treatment      | Experimental Treatment |
|                        | Period 1               | Period 2               |
| Experimental Condition | $s_{11}$               | $s_{12}$               |
| Control Condition      | $s_{21}$               | $s_{22}$               |

### 10.4.2 Weighting of evidence

To synthesize the sample statistics and treatment effect over both periods while taking into account the missing data structure, a weighting procedure can be used. The weights associated with each study condition and period combination are denoted by  $w_{ij}$ . The weights are equal to the number of observations used to calculate the corresponding test statistic. For example, if there are no dropout in Periods 1 and 2 but we do find respectively 500 and 600 positive serology tests at the end of Period 1 for the experimental condition and the control condition, then  $w_{.1}$  is 10.000 and  $w_{.2}$  is 8900. Because 500 people in Period 1 in the experimental condition had a positive serology test, the sample size for the control condition in Period 2 is reduced by 500. Aggregated statistics for the study conditions can be calculated by  $\bar{S}_1 + \bar{S}_2$ .

$$\bar{S}_1 = \frac{w_{.1} * (S_{11} - S_{21})}{w_{.1} + w_{.2}}$$

$$\bar{S}_2 = \frac{w_{.2} * (S_{12} - S_{22})}{w_{.1} + w_{.2}}$$

For every bootstrap sample,  $\bar{S}_1$  and  $\bar{S}_2$  can be computed and a variance estimate for  $\bar{S}_1 + \bar{S}_2$  can be obtained from this empirical distribution. Note that the weights also vary for each bootstrap sample depending upon the number of Period 1 infections that were sampled.

### 10.5 Analysis of Secondary Endpoint(s)

Secondary study endpoints mentioned in section 8.1.2 will be analysed and compared within the Intention-to-treat, Efficacy analysis and Partial compliance sets within each period. Where deemed relevant, analyses will also be executed within selected subsets of these analysis sets. Specific subsets will be listed within the Statistical Analysis Plan. Results will be presented in tables where possible. Where percentages are to be calculated, the number of subjects in the condition within the specified analysis (sub)set will be used as the denominator.

Where assumptions are met, Cochran-Mantel-Haenszel tests stratified by the risk strata will be performed in each period for multiple secondary endpoints, including:

- The number and percentage of subjects that obtained a red-light indicator by the applied algorithm at least once.
- The number and percentage of subjects with at least one positive SARS-CoV-2 virus test result during follow-up.

- The number and percentage of subjects that donated a blood sample for a SARS-CoV-2 antibody test at baseline, after the Learning Phase and after both periods.
- The number and percentage of subjects with a positive SARS-CoV-2 antibody test at baseline, after the Learning Phase and after both periods.
- The number and percentage of subjects with at least one positive SARS-CoV-2 virus test result during each period OR a positive SARS-CoV-2 antibody test result within those periods.
- The number and percentage of subjects without a positive SARS-CoV-2 virus test result during each period AND a negative SARS-CoV-2 antibody test result within those periods.
- The number and percentage of subjects that have reported experiencing each of the symptoms listed in the Ava COVID-RED app at least for one day during the study.
- The number and percentage of subjects that have reported experiencing each of the symptoms corresponding by the RIVM guidelines at least for one day during the study.
- The number of subjects who reported a positive SARS-CoV-2 virus test during the study and the percentage of subjects who reported a positive SARS-CoV-2 virus test during the study, with the number of subjects ever receiving a PCR test during the study as the denominator.

Where assumptions are met, t-tests will be performed in each period for multiple secondary endpoints, including:

- The average and median number of times a single subject obtained a red-light indicator by the applied algorithm.
- The average and median number of continuous days that each symptom in the Ava COVID-RED app was reported to be experienced.
- The average and median number of continuous days that each symptom corresponding to the RIVM guidelines was reported to be experienced.
- The average (and variance) number of days between a red-light indicator of the applied algorithm and the SARS-CoV-2 virus test result, stratified for tests done via the GGD and central laboratory, and also stratified for testing methodology.
- The average (and variance) number of days between a red-light indicator of the applied algorithm and the taking of a SARS-CoV-2 virus test, stratified for tests done via the GGD and central laboratory, and also stratified for testing methodology.

- Number of total SARS-CoV-2 virus tests taken by subjects, stratified for tests taken by GGD and/or central laboratory, and also stratified by testing methodology if applicable (PCR vs. antigen tests).
- The number of total positive SARS-CoV-2 virus tests and percentage of positive tests, with the number of total tests within the study taken as a denominator. This will also be stratified for the different testing methodologies if applicable.
- Average and median duration of Ava bracelet and/or Ava COVID-RED app use (number of days between first day of use and last day of use)
- Compliance rate: percentage of days (as compared to duration of use) that Ava bracelet data was synced to Ava COVID-RED app or symptoms were entered. Upon inspection of the data, other modes (like Poisson regression) will also be considered.

For other relevant endpoints (e.g. survival status of subjects at end of follow-up) appropriate statistical methods (e.g. survival analysis) will be used. Further details will be indicated within a separate statistical analysis plan.

